### Data management

The data of the participants will be included in an Excel database and then exported to SPSS version 18. The database will be shared between the data-collecting researchers and a responsible researcher. Patients will be coded according to the order in which they enter the survey following number allocation, corresponding randomization, collection of blood or feces, and begin or end (pre or post treatment). The procedures will be updated in the cadre ClinicalTrials.gov, ID: NCT03467282.

### Statistical analysis

For the quantitative variables, the comparison between the values obtained before and after the intervention will be performed by the *t* test for parametric samples (or Wilcoxon’s signed-rank test if the data do not satisfy the assumptions for this test); for the qualitative variables, the McNemar test will be used.

In the comparison of treatments for the quantitative variables, a delta value will be computed (value before − value after); the delta values will be compared between interventions using the *t* test for independent samples (or the Mann-Whitney *U* test). Delta values can be adjusted by age and other covariates by analysis of covariance. It will be considered statistically significant if *P* < 0.05. Statistical analysis will be performed in SPSS 18.0.

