### Outcomes

Primary outcome:
Modification in fibrosis level by elastography scores

Secondary outcomes:
Gut microbiota diversity assessed by metagenomic analysisIntestinal permeability assessed by claudin-3 and lipopolysaccharide (LPS) levelsInflammatory response evaluated by *TLR-4* gene expression and biomarker cytokeratin 18 (CK-18) and C-reactive protein (CRP) levelsComponents of the metabolic syndrome evaluated by anthropometry and laboratorial assessmentModifications in the parameters of sarcopenia evaluated by Dual-energy X-ray Absorptiometry (DEXA), bioelectrical impedance analysis (BIA), physical capacity, and myostatin, a negative regulator of muscle growth, and testosterone levels

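### Before-after tests share the P < 0.05 rule with the between-arm test, efficacy conclusions are not limited to the latter, and qualitative variables have no between-arm test

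*Protocol article*

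**What the plan says.** All of the following is in the protocol article.

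- **Statistical analysis, first paragraph.** "For the quantitative variables, the comparison between the values obtained before and after the intervention will be performed by the" t test, with Wilcoxon's signed-rank test as the fallback. Qualitative variables: "for the qualitative variables, the McNemar test will be used". Both are paired methods. The paragraph does not say whether they are run within each arm or on the arms pooled.
- **Statistical analysis, second paragraph.** "In the comparison of treatments for the quantitative variables, a delta value will be computed", and "the delta values will be compared between interventions using the" independent-samples t test or the Mann-Whitney U test. An optional adjustment follows: "Delta values can be adjusted by age and other covariates by analysis of covariance".
- **Significance rule.** "It will be considered statistically significant if" P is below 0.05. It appears once, after both sets of tests, and is restricted to neither.
- **Outcomes.** The primary outcome is "Modification in fibrosis level by elastography scores". The wording does not say whether the change is judged within an arm or between arms. The section on hepatic assessment describes the elastography result as a number in kPa, so it falls under the quantitative methods.
- **Study setting.** The trial is randomized, double-blind and placebo-controlled.

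**The concern.** In a placebo-controlled trial only the contrast between arms estimates the treatment effect. A paired test in the probiotic arm asks whether patients changed. They may do so through regression to the mean, repeated clinic contact or trial participation, with no help from the probiotic. Finding one arm significant and the other not does not amount to a test of the difference between them.

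The article plans both kinds of test at one threshold and does not say which supports a conclusion about the probiotic. A results paper could report a significant before-after change under probiotic and a non-significant one under placebo, and present the contrast as efficacy, without departing from the written analysis.

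For qualitative variables the problem goes further. The paragraph on comparing treatments is confined to quantitative variables, so McNemar's test is the only method named. The article does not list which outcomes will be analysed as qualitative, but its methods produce some classifications, such as sarcopenia status and gait speed below 0.8 m/s. A significant McNemar result on these cannot show a treatment effect.

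**Working it through.** The plan gives no error rate for its before-after tests, so there is no figure of its own to reproduce. The check asks how often the misleading pattern would arise if the probiotic did nothing.

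**Inputs**
- Planned total 46, with 10% added for losses (Sample size).
- Equal allocation is assumed, since the ratio is not stated: 46 / 2 = 23 per arm, and 23 × 0.9 = 20.7, about 21 evaluable per arm.
- Significance level 0.05 (Statistical analysis), taken as two-sided because the article does not say.
- Common true change *c* in both arms, in units of the SD of change. The article gives no value, so it is varied from 0 to 0.8.
- Before-after tests are taken as run within each arm, which is the natural reading but is not written out. Changes are taken as normal.

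**Formulas**
- Probability that a paired t test in one arm is significant: p(c) = P(|T| > 2.086), where T is noncentral t with 20 degrees of freedom and noncentrality c√21.
- The arms are independent, so P(probiotic significant, placebo not) = p(1 − p).
- The between-arm test of deltas has a true difference of c − c = 0, so its false-positive rate is 5% for every *c*.

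**Results with no treatment difference**

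| Common change *c* (SD) | p: probiotic arm significant | p(1 − p): probiotic significant, placebo not | Between-arm test |
|---|---|---|---|
| 0 | 0.05 | 0.05 × 0.95 = 5% | 5% |
| 0.3 | 0.26 | 0.26 × 0.74 = 19% | 5% |
| 0.43 | 0.47 | 0.47 × 0.53 = 25% | 5% |
| 0.5 | 0.59 | 0.59 × 0.41 = 24% | 5% |
| 0.6 | 0.74 | 0.74 × 0.26 = 19% | 5% |
| 0.8 | 0.94 | 0.94 × 0.06 = 6% | 5% |

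The product p(1 − p) cannot exceed 0.25. It reaches that at p = 0.50, which is *c* of about 0.45, and already rounds to 25% at 0.43.

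**Simulation check.** With 100,000 simulated trials per setting, the between-arm test was significant in 4.9% to 5.1% throughout. The pattern of probiotic significant and placebo not occurred in 4.7%, 19.2%, 25.1%, 24.2% and 5.9% of trials at *c* = 0, 0.3, 0.43, 0.5 and 0.8. In most of these trials the between-arm test was not significant: the pattern together with a non-significant between-arm test occurred in 3.2%, 16.9%, 22.7%, 21.9% and 4.8%.

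**Fall at large changes.** At 0.8 SD the pattern becomes rare only because both arms are then usually significant. The paired test in the probiotic arm, read alone, is significant in 94% of such trials.

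**The case against.** The strongest reply is that the plan already contains the right test. It has a separate paragraph for comparing treatments and assigns it to deltas between arms, with a valid test and optional covariate adjustment. The primary measure, in kPa, is covered by it. Describing change first and then comparing change is an ordinary order of presentation. This stands, and it rules out several stronger readings that a reader might infer:

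- *That the trial will declare efficacy from a before-after result.* No sentence says so. The P < 0.05 rule defines significance of a test and is not a rule for declaring a probiotic effect.
- *That the before-after tests have priority because they are listed first.* Order in the text is not stated priority.
- *That the sample size shows a within-arm intent.* The figures printed, 9.36 to 6.38, are a change in one treated group, but the same sentence cites a P value against placebo. Nor does the total fit a paired calculation. With an SD of change of √(1.9² + 1.5²) = 2.42 (zero correlation), a one-sample test at 90% power needs (2.42 × (1.960 + 1.282) / 2.98)² = 6.9, so 7 patients.
- *That the misleading pattern arises in 38% to 50% of trials.* Those are the chances that exactly one arm is significant, and half of them are trials in which only placebo is significant. Such trials could not support a probiotic claim.

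A further reply is that naming the deciding test is commonly left to an analysis plan that is not shown. That has force for silence alone. Here, however, the article itself sets out paired significance tests under the shared threshold, and for qualitative variables it names a paired test as the only method. Those are stated choices.

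It is also fair that a common change in both arms is conjecture. The visits every 45 days are for adherence, and no dietary treatment is described. The range in the working is therefore illustrative.

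**Conclusion.** The point holds as an unguarded route to a false claim and does not amount to a stated decision rule. The analysis of the primary outcome contains a valid between-arm test. What is missing is any statement that conclusions about the probiotic rest on it, while before-after p values are planned at the same threshold. For qualitative variables the gap is concrete, because no between-arm test is named.

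If the pattern of probiotic significant and placebo not were read as efficacy, the false-claim rate with no treatment difference would run from about 5% (no common change) to at most 25% (common change near 0.43 to 0.45 SD), falling to 6% at 0.8 SD. The between-arm test holds 5% throughout. These figures assume 21 evaluable patients per arm, equal allocation, two-sided tests within each arm and normal changes. The common change is an assumption throughout. The correction is worth making because it costs almost nothing and should be fixed before unblinding.

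**What to change.** Amend the Statistical analysis section as follows.

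1. State that conclusions about treatment rest on between-arm comparisons. For the primary outcome this is the difference between arms in change in liver stiffness (kPa) at week 24.
2. Report before-after changes within each arm as estimates with 95% confidence intervals, without p values and without efficacy claims.
3. Report secondary outcomes, including qualitative ones, as between-arm differences with 95% confidence intervals. For a binary outcome this could be the difference in proportions at week 24. McNemar's test would no longer be the only method for these variables.

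The cost is a change of wording. No extra patients, visits or measurements are needed. The sponsor gives up within-arm p values. The within-arm changes themselves are still reported.

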#### Sarcopenia

Sarcopenia will be determined following the European Consensus [25] considering muscle mass, muscle strength, and physical performance.

Muscle mass will be measured by the body composition assessment. DEXA (The GE Medical Systems Lunar Prodigy densitometer, Chicago, IL, USA) will be used for body-composition assessment. Fat and lean masses will be determined for the whole body and for body regions (trunk and limbs), as previously described [34]. Electrical bioimpedance (Biodynamics450®, Plainview, NY, USA) will be used to measure the percentage of fat, lean mass, and phase angle. Patients should be fasting for 4 h, not drink alcohol and/or caffeine, not have exercised in the last 12 h, not take diuretics the day before the test, not have a pacemaker in situ, and not be pregnant or menstruating. Patients will be questioned about the presence of significant diarrhea at the time of the examination to exclude the possibility of dehydration [35].

Muscle strength will be evaluated by the handgrip strength (dynamometry). Patients should be seated with their elbow flexed at 90° to hold the dynamometer (Jamar, Duluth, MN, USA) at its maximum strength for 3 s. There will be three repetitions with an interval of 1 min with the dominant hand. The highest strength will be recorded in kgF for classification [36].

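### Categorical secondary variables get only a before/after McNemar test, so the analysis as written cannot attribute a categorical change to the probiotic

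*Protocol article*

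**What the plan says.** The Statistical analysis section of the protocol article has two working paragraphs.

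- The first concerns change over time: "the comparison between the values obtained before and after the intervention will be performed by the" paired t test (or Wilcoxon signed-rank) for quantitative variables, and "for the qualitative variables, the McNemar test will be used".
- The second concerns the arms: "In the comparison of treatments for the quantitative variables, a delta value will be computed", and "the delta values will be compared between interventions using the" independent-samples t test or the Mann-Whitney test, with covariance adjustment as an option.

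One significance rule follows both paragraphs: "It will be considered statistically significant if *P* < 0.05". No section of the article names a between-arm test for categorical data.

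Variables that can be categorical are defined under Data collection methods. The Sarcopenia section says "Sarcopenia will be determined following the European Consensus", and it sets a gait speed under 0.8 m/s as marking risk. The Outcomes section lists components of the metabolic syndrome and parameters of sarcopenia as secondary outcomes. The primary outcome there is "Modification in fibrosis level by elastography scores".

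**The concern.** McNemar's test asks whether, among patients whose status changed, as many moved one way as the other. It makes no comparison between probiotic and placebo. A significant result in the probiotic arm combines any treatment effect with regression to the mean, the effect of regular visits and lifestyle change. The placebo arm is there to separate these from the treatment.

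For quantitative variables the plan makes that separation in its second paragraph. For qualitative variables it stops after the first. An analyst who follows the text would have a paired p-value, judged at 0.05, as the only inferential result for sarcopenia status. The Discussion presents sarcopenic parameters as part of what is new in this trial, so such a result could well be reported.

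**Working it through.** **Which variables have a between-arm test**

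| Variable type | Before/after test | Between-arm test |
|---|---|---|
| Quantitative | paired t or Wilcoxon | independent t or Mann-Whitney on the change; ANCOVA optional |
| Qualitative | McNemar | none stated |

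**Does the gap reach the primary outcome?** No. The section on hepatic structure and functional assessment says that the elastography result is a median reported as a number in kPa. The Sample size section works from a mean and SD. The article gives no elastography cut-offs or grades. The primary outcome is therefore quantitative and is covered by the second paragraph.

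**Size of the problem.** The plan prints no figure on this point to reproduce. Inputs:

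- From the Sample size section: 46 patients with a 10% loss allowance, so 46 / 2 = 23 per arm if balanced, and 23 × 0.9 = 20.7, about 21 per arm completing.
- From the Statistical analysis section: α = 0.05, taken as two-sided.
- Assumed: no treatment effect; 5% of patients worsen in each arm; 10% to 40% improve in each arm. The article gives no such rates.

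With b improving and c worsening in an arm, exact McNemar is p = 2 × P(X ≤ min(b, c)), X ~ Binomial(b + c, 0.5), capped at 1. Summing over all (b, c) gives π, the chance of significance in one arm. The arms are independent, so the chance of significance in the probiotic arm and not in the placebo arm is π(1 − π). For comparison, Fisher's exact test is applied between arms to the proportion improved.

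Results at 21 per arm, no treatment effect:

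| Improving in both arms | McNemar significant in one arm (π) | Probiotic arm only, π(1 − π) | McNemar, arms pooled | Fisher between arms |
|---|---|---|---|---|
| 10% | 0.6% | 0.6% | 5% | 1.3% |
| 20% | 10.9% | 9.7% | 39% | 2.3% |
| 30% | 35.0% | 22.8% | 77% | 2.3% |
| 40% | 61.5% | 23.7% | 95% | 2.0% |

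At 23 per arm the one-arm figures are 0.9%, 13.7%, 40.6% and 67.4%, and Fisher's test rejects in 1.6% to 2.5%.

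π rises with the background improvement rate although the treatment does nothing. Pooling the arms strengthens this, because it doubles the patients contributing to the same time trend. Fisher's test stays below 5% throughout.

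**One data set, 23 per arm**

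- Probiotic, 8 improve and 1 worsens: p = 2 × (1 + 9) / 2⁹ = 20 / 512 = 0.039.
- Placebo, 5 improve and 1 worsens: p = 2 × (1 + 6) / 2⁶ = 14 / 64 = 0.22.
- Between arms, 8 of 23 against 5 of 23 improved: Fisher p = 0.51.

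The paired tests look like one positive arm and one negative arm. The randomised comparison shows no evidence of a difference.

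**The case against.** Most of the trial is untouched. The Outcomes section describes its endpoints largely through measurements: stiffness, diversity, serum levels, gene expression, body composition and physical capacity. As measured values, all of these have a between-arm test. Sarcopenia status and the gait-speed cut-off are classifications in the data-collection text and are not themselves listed as outcomes. Metabolic syndrome is listed by its components, not as a status. This stands, and it limits the severity.

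Three stronger readings are tempting, and the documents do not support them.

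- *The primary outcome might be analysed as grades and so lack a between-arm test.* The word level in the outcome's wording invites this. But the article reports elastography in kPa and gives no grades. If ordered grades were used, the rank tests already named could take them; the standard McNemar test is for binary data.
- *The trial cannot attribute a categorical change to treatment.* The data are randomised and allow a valid comparison. The fault lies in the analysis as written, not in the design.
- *The plan carries a false-positive rate of about 25%.* Nowhere does the plan say that significance in one arm only will be read as an effect. Moreover, π(1 − π) cannot exceed 25%, so a figure near that is the worst case. At 10% improving it is under 1%. A high improvement rate also needs at least that share of patients to have the condition at baseline, and the article gives no prevalence.

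It can also be said that a condensed article leaves detail to a fuller protocol. That would answer silence. Here the article names the test for qualitative variables and, in words, restricts the treatment comparison to the other type. Whether McNemar is run per arm or pooled is not stated, but neither version compares the arms.

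**Conclusion.** The concern holds for categorical secondary variables. As written, the plan gives them a test of change over time and no test of probiotic against placebo, so a categorical change cannot be attributed to the probiotic on that analysis.

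The gap itself follows from the text alone. Its size depends on assumed rates: 5% worsening, 10% to 40% improving, no treatment effect, and about 21 completers per arm. On that range a McNemar result in the probiotic arm would be significant by background change alone in about 1% to 62% of trials, and in that arm only in about 1% to 24%. A between-arm Fisher test would reject in about 1% to 3%.

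Severity is minor to moderate. The primary outcome and the measured secondary outcomes already have a between-arm comparison.

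**What to change.** Add to the Statistical analysis section that:

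- binary variables at week 24 are compared between arms by logistic regression adjusted for baseline status, or by Fisher's exact test with a risk difference and 95% CI where counts are sparse;
- ordered categories are compared between arms by the Mann-Whitney test;
- McNemar results are descriptive and are not used to claim a treatment effect.

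The cost is one or two sentences and no new data. The Trial status section says that data are still being collected, so the rule can be fixed before unblinding.

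The comparison will be imprecise. At 23 per arm, 80% power (normal approximation) needs improvement of about 47% against 10%, 60% against 20%, or 71% against 30%. The interval should therefore be reported along with the p-value.

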### Randomization

The randomization will be performed through a simple, sequential, randomization plan generated online (using the randomization.com website).

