### Sample size

The sample size estimation was carried out in WINPEPI 11.20 (Brixton Health, Israel), based on data from Eslamparast et al. [29] that found a mean reduction in fibrosis score of 9.36 ± 1.9 to 6.38 ± 1.5 in NAFLD patients taking symbiotic supplementation (*P* < 0.001, compared to placebo). Thus, considering a power of 90% and a significance of 5%, adding 10% to compensate for eventual losses, it will be necessary to include 46 patients with NAFLD in the present study.

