#### Hepatic structure and funcional assessment

Liver fibrosis will be assessed by transient elastography (FibroScan). The Controlled Attenuation Parameter (CAP) is a tool based on the FibroScan, used for the detection and quantification of liver steatosis. The elastic wave propagates through the liver at a certain rate dependent on hepatic stiffness (fibrosis). The higher the velocity, the greater the stiffness, measured in kilopascals (kPa), and the greater the extent of the fibrosis. The median is considered the most representative value, being the immediate result, and is numerical and expressed in kPa [30].

In addition, blood samples will be collected for the evaluation of the genetic expression of biomarker *TRL4*, and CK-18, which are directly associated to liver inflammation.

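### The default between-arm test is an unadjusted comparison of deltas; baseline-adjusted ANCOVA should be fixed as primary, for efficiency and prespecification

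*Protocol article*

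**What the plan says.** Under Statistical analysis, the protocol article defines a delta for each quantitative variable as the value before minus the value after, and says that "the delta values will be compared between interventions using the" independent-samples t test, with Mann-Whitney as the alternative. The next sentence is permissive: "Delta values can be adjusted by age and other covariates by analysis of covariance". Age is the only covariate named, the rest are left open, and no sentence says whether the adjusted or the unadjusted result is primary.

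This rule governs the primary outcome. Under Outcomes that is "Modification in fibrosis level by elastography scores", and the section on hepatic assessment says that the elastography result "is numerical and expressed in kPa". The Abstract (Methods) has the assessments done at baseline and again after 24 weeks, so the baseline value is due to be collected.

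Nothing stated in the design balances baseline stiffness: "The randomization will be performed through a simple, sequential, randomization plan generated online", with no stratification mentioned, for 46 patients.

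**The concern.** A raw change score stays correlated with its own baseline. An analysis that ignores this carries baseline noise into the treatment contrast, so its standard error is larger than the data require. If the arms also happen to differ at baseline, regression to the mean shifts the delta contrast in a predictable direction, and the stated test does nothing about it.

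The second issue is prespecification. The text allows a t test, a Mann-Whitney test, or ANCOVA with covariates yet to be chosen, and ranks none of them. With 46 patients these can give different P values for the one primary question. Recruitment was almost complete when the article was written (45 patients started, per Trial status), so the analysis is one of the few places where precision can still be gained.

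**Working it through.** **Inputs from the protocol article**
- Planning figures (Sample size): "mean reduction in fibrosis score of 9.36 ± 1.9 to 6.38 ± 1.5" in supplemented patients of a cited study, a before-to-after change of 9.36 − 6.38 = 2.98.
- "considering a power of 90% and a significance of 5" percent; two-sided testing is assumed.
- Total 46 after "adding 10% to compensate for eventual losses". 46/1.10 = 41.8, so about 42 evaluable, or 21 per arm if allocation is 1:1 (assumed).

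**Assumptions not in the documents**
- The correlation rho between baseline and week 24, shown from 0.3 to 0.9.
- A net between-arm difference of 1.5, for illustration.
- SD 1.9 at both times. The SD of 1.5 is quoted only for supplemented patients at follow-up, so it is not applied to both arms.

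**The plan's own figure.** The stated 46 does not reproduce. A two-sided comparison of means with difference 2.98 needs 14 to 20 patients including losses (SD 1.5 to 1.9), or 31 to 32 using the SD of change at rho 0. That is a separate matter, and nothing below depends on it.

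**Step 1: relative efficiency.** With a common SD s, the per-patient variance is 2s²(1 − rho) for the delta and s²(1 − rho²) for the baseline-adjusted outcome. The ratio is (1 − rho²)/[2(1 − rho)] = (1 + rho)/2. The patients needed to match 42 under the delta test are 42 × ratio, rounded up. If the delta test has 90% power, ANCOVA has Φ[(1.960 + 1.282)·√(2/(1 + rho)) − 1.960].

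| rho | Variance ratio | ANCOVA patients matching 42 | ANCOVA power if delta test has 90% |
|---|---|---|---|
| 0.3 | 0.65 | 28 | 98.0% |
| 0.5 | 0.75 | 32 | 96.3% |
| 0.7 | 0.85 | 36 | 94.0% |
| 0.9 | 0.95 | 40 | 91.4% |

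**Step 2: illustrative power.** Net difference 1.5, SD 1.9 at both times, 21 per arm. The SD of the delta is 1.9·√[2(1 − rho)], and the ANCOVA residual SD is 1.9·√(1 − rho²). The noncentrality is 1.5/(SD·√(2/21)), with √(2/21) = 0.309, referred to the noncentral t distribution.

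| rho | SD of delta | ANCOVA residual SD | Power, delta | Power, ANCOVA |
|---|---|---|---|---|
| 0.3 | 2.25 | 1.81 | 56% | 74% |
| 0.5 | 1.90 | 1.65 | 70% | 82% |
| 0.7 | 1.47 | 1.36 | 90% | 94% |

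Both tables ignore the small loss from estimating the covariate slope. On average this multiplies the ANCOVA variance by about 1 + 1/(42 − 4) = 1.03.

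**Step 3: the same check at 2.98.** With the quoted SDs and rho 0, the SD of change is √(1.9² + 1.5²) = 2.42. The delta test with 21 per arm then has about 97% power, and more at any positive rho.

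**Step 4: chance imbalance.** The standard error of the baseline difference is 1.9 × 0.309 = 0.59. A gap above half an SD (0.95) is 0.95/0.59 = 1.62 standard errors, a two-sided probability of 0.105. Given such a gap, the expected delta contrast moves by (1 − rho) × 0.95: 0.67, 0.48, 0.29 or 0.10 at rho 0.3, 0.5, 0.7 or 0.9. With the before-minus-after sign, the arm that starts higher appears to improve more.

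**The case against.** Several objections have force.

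- **The test is valid.** A reader might infer that the delta comparison is biased. The documents do not support that. Under randomisation it is unbiased on average and keeps its type I error; regression to the mean acts only conditionally on an observed baseline gap. Nor is a serious gap likely: Step 4 gives about one chance in ten of exceeding half an SD.
- **The gain depends on an unknown.** At rho 0.9 with equal SDs it nearly disappears. One could quote a rise from 78% to 95% by using SD 1.9 before and 1.5 after in both arms, rho 0.5 and a difference of 1.5. But the 1.5 SD is reported only for supplemented patients, and the difference and rho are assumptions. With SD 1.9 throughout, the same case gives 70% to 82%. Carrying a cited NAFLD study's SDs to this NASH population is a further assumption in either calculation.
- **On the planning contrast, little is lost.** This is correct at 2.98. But 2.98 is a before-to-after change within supplemented patients, and the net difference from placebo may be smaller. That is where the efficiency counts.
- **Details may sit in an analysis plan that is not shown.** ANCOVA is provided for, and the open covariate wording could include baseline. A covariate list could properly be left to that plan. What can be criticised is what the article itself fixes: an unadjusted default, with adjustment as an unranked option.
- **Post-randomisation covariates and skewness.** A reader might infer that the open wording is meant to admit post-randomisation variables, or that kPa values must be log-transformed. The text does not propose the former, and nothing in it shows skewness.

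**Conclusion.** The point stands as an improvement in efficiency and prespecification that should be made, not as an error that invalidates the primary result. The stated default is less precise than baseline-adjusted ANCOVA by a factor (1 + rho)/2 in variance with equal SDs, equivalent to between 5% and 35% of the sample for rho from 0.9 down to 0.3. The power figures for a difference of 1.5 are illustrations that rest on an assumed effect, an assumed correlation, a common SD of 1.9 and 21 evaluable patients per arm. The absence of a designated primary result among the permitted analyses follows from the text alone and needs none of these assumptions.

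**What to change.** State in Statistical analysis that the primary between-arm comparison is an ANCOVA of week-24 elastography in kPa on treatment, with baseline elastography as a fixed covariate. Using the delta as the response gives the same treatment estimate once baseline is in the model. Name any further covariates, such as age, before unblinding, and restrict them to variables measured at baseline. Keep the unadjusted delta t test or Mann-Whitney test as a sensitivity analysis. A log scale is optional; if it is wanted, choose it in advance. The same model can be used for the quantitative secondary outcomes.

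The cost is a change of wording and one degree of freedom for baseline (one more for age, if used). No new data, visits or patients are needed, and the article already provides for ANCOVA.
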